### Feeding protocol

Mothers will determine the timing of meals according to their own schedule. However, they will feed the foods according to a prescribed recipe and colour rotation to improve standardisation and ensure infants are exposed to a variety of flavours (Fig. 2). On recording days (the first and last 4 days) mothers must only provide one colour per day, starting with green. On other days, colours rotate per meal. No meat is provided during the first 4 days to standardise infants’ very first tastes. To cater to individual infant needs, mothers can provide as many meals as they need per day.

**Fig. 2 Fig2:**
[figure not shown]
Food rotations for intervention and control group, either per day (recording days) or per meal (other days). Foods will be labelled by colour and none list the ingredients but mothers are reassured that the foods align with New Zealand infant feeding guidelines. The code A or B act as identifiers for researchers

The rotation order of foods offered for the intervention group is determined by sugar content, starting with the first food containing the lowest sugar per 100 g. This should help to expose infants to more bitter flavours first. The order is matched to the intervention group to improve standardisation and ensure vegetables, such as spinach, will be introduced at the same time where possible. Instructions on feeding style and environment will be provided, for example, “let baby lead”, “use a spoon”, and “choose a quiet time without distractions”. At 9 months of age, each group will be offered a brassica (broccoli), green leafy vegetable (spinach) then sweet fruit (pear) over 3 consecutive days (one per day). These will be labelled meal A, meal B, and meal C, respectively. Infants should not have had solid food within 1 h prior to trying the meal. Assessment of intake of each food should determine whether a “vegetables first” approach to complementary feeding results in higher intake of a brassica or green leafy vegetable at 9 months of age compared to a control group.

### Education session

To standardise the feeding sessions as much as possible, all mothers will receive a 40-min education session on appropriate infant feeding practices during their first visit, delivered by the primary investigator who is also a New Zealand registered Dietitian. Topics include identifying the signs of developmental readiness to start complementary feeding, responsive feeding, and appropriate breast/formula milk feeding. Instructions for the study protocol and food diary will also be discussed in detail. A series of educational resources, including three infant feeding fridge magnets designed for the study will be provided during the session and mothers will be encouraged to visit the study website to view additional resources. After completion of the 4-week intervention, all mothers receive the Ministry of Health *Eating for Healthy Babies and Toddlers/Ngā kai tōtika mō te hunga kōhungahunga* [52] and Beef and Lamb New Zealand *Fuelled by Iron* [53] pamphlets to assist infants’ transition to family foods.

### Randomisation, blinding, and concealed allocation

Eligible and consented mother-infant pairs will be randomly allocated to either the intervention or control group, having been stratified by infant gender and using a random number generator by the research trials manager who is not involved in the study design and outcome analysis. In accordance to block randomisation with a 1:1 allocation, for every block of eight participants, four will be allocated to each arm of the trial, with the block size concealed until the primary endpoint is analysed. Allocation concealment will be ensured, as the release of the randomisation code occurs only until the participant has been recruited into the trial, which is after consent and baseline measurements have been completed. After assignment, researchers will not be blinded given their necessary involvement in the food product development and subsequent familiarity with food characteristics (e.g. colour). While participants will be provided with an information sheet that lists all the types of fruit and vegetables included on the study, they will be blinded to the specific foods allocated to them as foods are labelled generically (e.g. “Green A” rather than “spinach/potato”). They will also be unaware of the RCT design, so do not know specific differences between feeding regimes. In an emergency where breaking of the study blind is needed, plans are in place for the principal investigator to reveal the treatment assignment for a given participant.

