### Video coding tool

During the intervention, mothers will be asked to video record their infant trying each study food at home for the first time in week 1, then again in week 4 without the researcher present. This provides a total of eight videos. When infants turn 9 months old, mothers will video record their infant at home trying meal A, B, and C. Each participant will be given access to their own secure online shared OneDrive file to upload their videos. To assess rate of acceptance, the videos will be coded using the coding tool described in Fig. 4. Rate of acceptance is the judgement made on how readily the infant accepts the spoon offered and is a measure of wanting. This outcome measure will be included because liking (hedonic drive) and wanting (motivation to eat) are considered interconnected components of food reward and pleasure but can be measured separately [61–63]. The coding tool is based on prior studies [40, 64], but with further consultation with the researchers, the addition of “grabs spoon to self-feed” as an indicator of early acceptance, as well measurable spoon distances are included to improve accuracy and standardisation. Coding will be completed by an independent researcher to reduce bias.

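### The block size is called concealed where one fixed block of eight is printed, and the video coder is promised to be independent but not masked, although masked coding at 9 months is feasible

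*Protocol article*

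**What the plan says.** On allocation, the section Randomisation, blinding, and concealed allocation sets out a 1:1 scheme:

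- Participants are allocated "having been stratified by infant gender", in fixed blocks: "for every block of eight participants, four will be allocated to each arm of the trial, with the block size concealed".
- This concealment is to last up to the analysis of the main outcome. The article does not say from whom the size is concealed.
- The list is produced by a "research trials manager who is not involved in the study design and outcome analysis".
- Concealment is presented as assured because each code is released only once the participant is recruited, "which is after consent and baseline measurements have been completed".
- On the blinding of staff the section says: "After assignment, researchers will not be blinded given their necessary involvement in the food product development". Under Feeding protocol, the legend to Fig. 2 adds that the A/B food codes identify the arm to researchers.

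On the videos, the section Video coding tool says "Coding will be completed by an independent researcher to reduce bias". Table 2 also names an independent researcher as coder and lists rate of acceptance among the primary outcomes; the Abstract lists wanting as secondary. Neither place says whether the coder knows the allocation. Mothers upload clips to one online file per participant, and Data handling describes the folder as labelled by subject number.

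**The concern.** Two separate safeguards are worded more strongly than the described procedures can support.

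First, releasing each code late hides the current code. It does not stop the next one being worked out from earlier ones when blocks are fixed and past allocations are visible. Researchers see every past allocation, and the only stratifier is known before randomisation. A foreseeable allocation allows enrolment or its timing to be chosen selectively.

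Second, independence is not masking. The reason given for not blinding researchers is their familiarity with the study foods. That reason has no force for the 9-month clips, where both arms eat the same broccoli, spinach and pear meals. Rate of acceptance is a judgement about how readily the infant takes the spoon. It is also the only food-acceptance measure in Table 2 that mothers do not report themselves, so detection bias would weaken the trial's one independent check on maternal report.

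**Working it through.** The article gives no predictability figure, so there is none of its own to reproduce.

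**Inputs.** Block of 8, 4 per arm, two gender strata, researchers unblinded (Randomisation section). Total 120 (Abstract), or 2 × 65 = 130 (Participants).

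**Certain allocations per block.** A 4:4 block has C(8,4) = 70 equally likely orders. An allocation is certain once either arm has used its four places.

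- Positions 1 to 4: 0
- Position 5: 2 × C(4,4)/70 = 2/70 = 2.9%
- Position 6: 2 × C(5,4)/70 = 10/70 = 14.3%
- Position 7: 2 × C(6,4)/70 = 30/70 = 42.9%
- Position 8: 2 × C(7,4)/70 = 70/70 = 100%

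The sum is 112/70 = 1.6 of 8, or 20%. This agrees with the closed form 1/(m+1) with m = 4 places per arm.

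**Best guess.** Someone who always guesses the arm with more places left is right for 66.6% of allocations, against 50% by chance (enumeration of the 70 orders).

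**Over the trial, two equal gender strata:**

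- N = 120: 60 per stratum = 7 full blocks + 4. The last 4 positions add nothing, so 2 × 7 × 1.6 = 22.4 (18.7%).
- N = 130: 65 per stratum = 8 full blocks + 1, so 2 × 8 × 1.6 = 25.6 (19.7%).
- For gender splits from 40:60 to 60:40, the share across both totals runs from 18.5% to 20.0%.

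**Effect of varying the blocks.** Simulation of 2,000 lists of 64 allocations, with the set of sizes known but not their order:

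| Block sizes | Certain | Best guess right |
|---|---|---|
| 8 only | 20.0% | 66.6% |
| 4 or 8 | 7.3% | 67.8% |
| 4, 6 or 8 | 2.2% | 67.8% |

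Varied blocks remove most of the certainty. They do not lower the best-guess rate.

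**What the clips show.**

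| Clips | Foods | Can the food reveal the arm? |
|---|---|---|
| Weeks 1 and 4 (Video coding tool; Table 1) | Each study food; orange only in control, Kākāriki only in intervention | Yes |
| 9 months (Feeding protocol) | Meals A, B and C, the same in both groups | No |

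All clips from one infant go to that infant's own file. A coder who worked through a folder in time order would learn the arm from the early clips before rating the 9-month ones.

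**The case against.** **On allocation**, a reader might infer that recruiting staff knew the block size and that a fifth of allocations were in fact foreseen. The article does not support that. It says the size is concealed and that someone outside design and outcome analysis makes the list. The evidence for knowledge is that the size is printed in an article dated 26 July 2021. Data collection ends in October 2021, so an infant starting at 4 to 6 months would have to begin by about May to July 2021 to reach 9 months in time. Publication therefore came at or near the end of enrolment and could hardly have exposed many later allocations. Opportunity is also narrowed by self-registration on a website, an online eligibility questionnaire, and release only after baseline. All of this stands, and it makes the one-in-five figure conditional. It does not reconcile the concealment claim with fixed blocks and unblinded researchers.

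**On the videos**, a reader might infer that the coder is unmasked. The text does not say so, and nothing shows that the coder worked on food development. Nor is the video the trial's only outcome not reported by mothers: Table 2 also lists researcher-measured anthropometry and laboratory blood results. It could further be said that coder access and clip order belong in the full protocol. Silence alone would indeed be no finding. But the article names independence as its safeguard against bias, and the storage it describes leaves a route by which an independent coder could still learn the arm.

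**Conclusion.** The point holds in a limited form.

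- **Concealment.** The assurance is too strong for one fixed block of eight within gender and unblinded researchers. The size is 20% certain allocations per complete block, or about 22 of 120 or 26 of 130. This assumes that the person enrolling knows the block size and tallies allocations within each gender stratum. Whether anyone did is not established.
- **Video coding.** Masking is not stated, the week-1 and week-4 clips can reveal the arm, and the 9-month clips do not reveal it through the food. Masked coding at 9 months is therefore feasible and should be secured. No size of bias can be calculated from the article. The weighed-intake outcome, recorded by mothers who are blinded to their allocated foods, is not touched by this second part.

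The coding part is the more useful to act on, because it can be applied to any 9-month clip not yet coded, even if enrolment is over.

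**What to change.** 1. **Video coding tool.** State that the coder has no access to allocation and receives the 9-month clips under a separate code, not the subject number, in random order across participants. The coder should finish them before seeing any week-1 or week-4 clip, or should never see those clips. Cost: relabelling and a coding-order instruction, plus a second coder only if the team wants the early clips kept apart altogether.
2. **Allocations still to be made, if any.** The trials manager should use randomly varied block sizes (for example 4, 6 and 8) within gender, not disclosed to recruiting staff. This cuts certain allocations to about 2% but leaves the best-guess rate at about 67–68%. Cost: a new list and slightly looser balance within gender.
3. **Infants already allocated.** Replace the concealment claim with a statement of who knew the block size and when. Cost: wording only.

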### Data collection

Mothers will be emailed the links to the online demographics, baby behaviour, and pregnancy/lactation food frequency questionnaires to complete at home before their first visit to the HNRU at which other baseline data (infant anthropometry and blood samples) will be collected. The 4-week intervention and primary data collection (mother reported infant vegetable liking and intake, video-recorded meals) will take place in the infant’s home environment from May 2019 to October 2021. Follow-up data (anthropometry and/or blood samples) will be collected at 9, 12, and 24 months of age at the HNRU; home visits will be available as required. In the instance where visits are not possible, mothers will be asked to provide current infant growth measurements (following standardised instructions given by the researcher) and food diaries by email or post. Virtual meetings using Zoom or Skype will be available for additional support. Additional child vegetable/fruit liking and food frequency questionnaires will be completed by mothers at home when their infant is 9, 12, and 24 months old. To the extent possible, we will continue to collect data for all outcome measures for participants who discontinue or deviate from the intervention protocols, while anticipating and planning for missing data. Given the potential for this cohort to provide valuable data for future early life nutrition research, additional outcome measures will be collected. These include mothers’ iron status/vitamin D status (at baseline), infants’ vitamin D status (at baseline), and infant stool samples for microbiota analysis (pre- and post-4-week intervention, and all follow-ups). Such data may be useful to assess maternal iron status 6 months post-partum or infant vitamin D status and links to the microbiome. Table 2 outlines the primary study outcome measures and testing methods. Figure 3 provides the schedule of enrolment, intervention, and assessment.

**Table 2 Tab2:** Summary of the study outcome measures and methods

Variables	Method
Primary outcomes	
Vegetable liking	Liking tool (Appendix A). Completed by mother at home
	Rate of acceptance video coding tool. Mother video-records meals. Independent researcher codes infant behaviours
	Child vegetable and fruit liking questionnaires. Completed online by mother
Vegetable intake	Weighed food diary. Completed by mothers at home
	FFQ. Completed online by mother
Blood analysis^a^	
Infant iron studies^b^	“Heel prick” test by phlebotomist at Massey University or home
Infant vitamin D	“Heel prick” test by phlebotomist at Massey University or home using *Whatman card*
Mother iron/vitamin D	Venous blood sample collection by phlebotomist at Massey University
Other measures	
Infant anthropometry	Head circumference: paper measuring tape, widest part of head, three measures, select largest measurement to the nearest 0.1 cm; length: infant length board; weight: infant electronic weighing scales, no nappy; measured by researcher at Massey University or participant home
Demographics	Completed online by mother
Mother diet	Pregnancy and lactation FFQ and FCQ. Completed online by mother
Baby eating behaviour	Baby eating behaviour questionnaire [54]. Completed online by mother
Compliance	2-min check-in questionnaires. Completed online by mother

^a^Analysed by LabTests, Auckland

^b^Serum ferritin, C-reactive protein (CRP), haemoglobin

*FFQ* food frequency questionnaire, *FFQ* food frequency questionnaire, *FCQ* food choices questionnaire

**Fig. 3 Fig3:**
[figure not shown]
Schedule of enrolment, interventions, and assessments. According to the SPIRIT statement: Defining Standard Protocol Items for Clinical Trials. *t,* timeline; *w,* week; *FFQ,* food frequency questionnaire; *preg,* pregnancy; *lact*, lactation; *FCQ,* food choices questionnaire; *Q,* questionnaire

### Weighed food diary

Mothers will complete a 4-day weighed food diary during the first and last 4 days of the 4-week intervention to primarily measure infant food intake (grammes). In alignment with other studies [33–39, 55–57], this will involve weighing the food before and after consumption using provided digital scales and completing the food record sheet. Estimated spills or food fallen on the bib will be recorded. The greater amount of food eaten may indicate a greater preference or acceptance for that food. In addition, the diary collects data for breast/formula milk feeding, meat consumption, and medication/supplements. Mothers can report factors that may have affected infant feeding each day (e.g. teething, unwell).

The diary is designed specifically for this study and includes a liking tool to assess the degree that infants like the study foods (see Liking tool). Combining these tools into one booklet should reduce participant burden and improve data collection. Detailed and visually appealing instructions on the feeding environment and protocol, such as food rotation and video-recorded meals, are included. Food diaries for each group differ only by the allocated foods mentioned; for example, instructions for the orange food do not feature for the intervention group diary. Week 1 and week 4 diaries also differ slightly by the removal of irrelevant instructions; for example, the week 4 diary excludes the instruction “After the first four days…”. A similar 3-day weighed food diary will be provided at 9 months of age but includes the option to list any other vegetables or fruits eaten that day.

Weighed food records are considered the best estimate food intake for children aged 0.5 to 4 years [58]. The use of 4- and 3-day weighed food diaries should help to reduce participant burden that is typically associated with those of greater durations (e.g. a 7-day food diary) without compromising accuracy [59, 60]. These durations also fit well with the protocol; for example, three tests meals offered over three consecutive days at 9 months of age is appropriately measured by a 3-day food diary.

### Liking tool

The liking tool for our study is adapted from the new in-home validated elaborate method to assess infant liking of vegetables [41]. The tool asks mothers to use a form to report positive and negative behaviours for each spoon offered for the first nine spoons in their home environment, then rate how much they thought their infant liked the food after each triplet of spoons (i.e. 3 x 3 spoons), then again at the end of the meal. After piloting the tool with a small group of New Zealand mothers and with further expert consultation it was agreed that a pictorial 5-point liking scale (1 = dislikes very much to 5 = likes very much), and a list 10 positive and 10 negative behaviours per spoon, which mothers can tick as they occur would reduce participant burden. The greater percentage of positive behaviours recorded may indicate greater liking, while an average score of at least 4 on the liking scale should indicate that the food is liked. It is required that a researcher provides mothers with additional guidance on feeding environment, feeding style to adopt, when to terminate the meal (three consecutive refusals), and the list of cues related to liking/disliking. These are adapted to align with New Zealand infant feeding guidelines [1], for example, the instruction to minimise verbal communication during feeding is removed as this conflicts with recommendations to interact with and talk to the child at meal times.

### Video coding tool

During the intervention, mothers will be asked to video record their infant trying each study food at home for the first time in week 1, then again in week 4 without the researcher present. This provides a total of eight videos. When infants turn 9 months old, mothers will video record their infant at home trying meal A, B, and C. Each participant will be given access to their own secure online shared OneDrive file to upload their videos. To assess rate of acceptance, the videos will be coded using the coding tool described in Fig. 4. Rate of acceptance is the judgement made on how readily the infant accepts the spoon offered and is a measure of wanting. This outcome measure will be included because liking (hedonic drive) and wanting (motivation to eat) are considered interconnected components of food reward and pleasure but can be measured separately [61–63]. The coding tool is based on prior studies [40, 64], but with further consultation with the researchers, the addition of “grabs spoon to self-feed” as an indicator of early acceptance, as well measurable spoon distances are included to improve accuracy and standardisation. Coding will be completed by an independent researcher to reduce bias.

**Fig. 4 Fig4:**
[figure not shown]
Video coding for rate of acceptance. Images provided with written permission from the participating subjects

### Questionnaires

A total of nine online questionnaires specifically developed for this study are to be completed by mothers via the survey software tool Qualtrics™. Researchers will check all answers for completeness.

#### Eligibility questionnaire

A 5-min eligibility questionnaire ensures that only infants that meet the inclusion criteria will be included.

#### Demographics questionnaire

A 10-min demographics questionnaire collects information at baseline on mother and infant date of birth, ethnicity, medical history, geographical location, mothers’ education level, and parity.

#### Pregnancy/lactation food frequency questionnaire (FFQ) and food choices questionnaire (FCQ)

As the mother’s diet may predict infant liking and intake of vegetables, a FFQ asking about mothers’ intake of vegetables and fruit during pregnancy and lactation is adapted from an existing New Zealand validated FFQ [65]. An accompanying FCQ gains further insight on other dietary habits, such as foods avoided. These questionnaires are peer-reviewed by three experts in the nutrition and dietetics field and pilot tested with 14 new mothers. Their feedback informed minor wording changes to increase readability and acceptability, thus improving content validity; each questionnaire requires 15–20 min to complete at baseline.

